Fibroblast activation protein (FAP) is a transmembrane protein that can be upregulated in solid tumors, including epithelial carcinomas [31–33]. In most tumors in which FAP is present, FAP is not directly expressed by the cancer cells themselves but by cancer-associated fibroblasts (CAFs), which represent a major part of the gross tumor volume. In 2018, the first results of [^68^Ga]Ga-FAPI PET/CT were published, with promising results both in animal cancer models and in cancer patients [32, 34, 35]. In pathological studies of human cancer tissue, FAP expression has been detected in 85–97% of ovarian cancers, both in serous and mucous subtypes. Moreover, FAP is absent/low in normal ovarian tissue and under benign conditions [33, 36–38]. Immediately after the development of the FAPI, the clinical value of FAPI PET/CT in OC patients was highlighted by several case reports in which FAPI PET/CT detected far more peritoneal metastases than [^18^F]FDG PET/CT [39–41]. Additionally, FAPI uptake in ovaries does not seem to be affected by the menstrual cycle, as is the case with [^18^F]-FDG [42, 43].

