**Fig. 1 Fig1:**
[figure not shown]
FAPI PET in ovarian cancer study design and flow

[^68^Ga]-Ga-FAPI-46 PET/CT data will be interpreted after enrollment of all patients and compared to the [^18^F]-FDG PET/CT data. Histopathology of the resected specimens and biopsies will serve as a reference standard for calculating the diagnostic accuracy. For suspicious lesions not confirmed by histopathology, other imaging modalities (US, MRI, CT), biochemistry, and medical records will be used for classification. The clinical impact of [^68^Ga]Ga-FAPI-46 PET/CT, both at primary staging and post-NACT staging, will be evaluated at a retrospective tentative MDT with the participation of an onco-gynecological surgeon, an oncologist, a pathologist, and a nuclear medicine physician, all of which specialize in the treatment of ovarian cancer. The tentative MDT will be performed retrospectively and therefore has no influence on the actual treatment of patients; moreover, the MDT differs from the clinical MDT, as clinicians will present study-related [^68^Ga]Ga-FAPI-46 PET/CTs instead of [^18^F]FDG PET/CTs. The study flow is depicted in Fig. 1.

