### Study population

#### Sample size and patients

Patients with biopsy-verified OC prior to the gynecological cancer MDT *or* highly suspected to have OC (based on all information presented at the gynecological cancer MDT) will be recruited until a total of 50 patients with histopathologically confirmed OC have been included. The upper limit of recruited patients is set at 60. Recruitment will take place at an outpatient clinic related to the Dept. of Gynecology and Obstetrics Aalborg University Hospital (Aalborg UH) by trained staff in accordance with national requirements [53]. Because an official sample size calculation is not feasible due to former study limitations, e.g., highly selected patients and lack of histopathology of metastases, the desired number of participants is based on the possibility of recruiting patients within 1.5-2 years at our institution, and more importantly, valid estimates of diagnostic accuracy are obtainable with the planned number of patients in an unselected consecutive cohort. Approximately 25 patients are estimated to undergo direct surgery after [^68^Ga]Ga-FAPI-46 PET/CT (Group A), and 25 patients will undergo NACT followed by a second [^68^Ga]Ga-FAPI-46 PET/CT (Group B). The recruitment strategy is based on unpublished clinical data from our institution and from published literature, where approximately 10–15% of the patients with highly suspected OC (based on all available information at MDT) had other non-OC malignancies or rarely benign conditions upon histopathology, e.g., endometriosis, gastric cancer (i.e., Krukenberg tumors), and colorectal cancer [24, 54].

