### Diagnostic accuracy

[^68^Ga]Ga-FAPI-46 PET/CT images will be independently interpreted under standardized conditions by two experienced nuclear medicine physicians, considering the currently known pitfalls in FAPI imaging [57–59]. The interpreters will be blinded to all clinical information regarding the patients except for the cancer diagnosis. Any disagreements that arise will be resolved through a consensus-based approach. Likewise, the [^18^F]FDG PET/CTs will be interpreted under standardized condition by experienced nuclear medicine physicians. ceCTs performed at primary staging and at post-NACT staging is part of the PET/CT procedure and will also be available for the interpreters and be used for deeming malignancy in suspicious lesions with low [^18^F]FDG / [^68^Ga]Ga-FAPI-46 uptake.

The correlations of the PET/CT results with histopathology, estimated sensitivities, specificity, PPV, and NPV for [^68^Ga]Ga-FAPI-46 PET/CT and [^18^F]FDG PET/CT findings will be compared for primary tumors, lymph nodes and distant metastases (e.g., peritoneal metastases). Ultimately, the diagnostic accuracy of [^68^Ga]Ga-FAPI-46 PET/CT and [^18^F]FDG PET/CT will be compared at primary staging and post-NACT-staging. Suspicious tumor lesions revealed on [^68^Ga]Ga-FAPI-46 PET/CT lacking histopathological confirmation will be evaluated using available routine diagnostic images ([^18^F]FDG PET/CT, UL, MR, ceCT), medical records, and laboratory tests. Furthermore, correlating [^68Ga^]Ga-FAPI-46 PET/CT at post-NACT staging with histopathology will be useful for assessing the feasibility of [^68^Ga]Ga-FAPI-46 PET/CT after chemotherapy.

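### Patient-level laboratory values help label individual lesions without histology, although they cannot separate a malignant from a benign focus in a patient with confirmed ovarian cancer

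*Protocol article*

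**What the plan says.** The Study flow overview section of the protocol article (text below Fig. 1) sets the main rule: "Histopathology of the resected specimens and biopsies will serve as a reference standard for calculating the diagnostic accuracy". It then gives the fallback: "For suspicious lesions not confirmed by histopathology, other imaging modalities (US, MRI, CT), biochemistry, and medical records will be used for classification".

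The Diagnostic accuracy section states the fallback again, with two differences. It speaks only of suspicious lesions on FAPI "PET/CT lacking histopathological confirmation will be evaluated using available routine diagnostic images", and its source list includes one of the two tests under comparison: "FDG PET/CT, UL, MR, ceCT), medical records, and laboratory tests".

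Accuracy is assessed below the level of the patient: "findings will be compared for primary tumors, lymph nodes and distant metastases (e.g., peritoneal metastases". The target cohort consists of patients known to have the disease, who are "recruited until a total of 50 patients with histopathologically confirmed OC have been included", with a recruitment cap of 60.

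Two further statements decide which lesions need the fallback. The FAPI result is not available to the treating physician (Study flow overview), and the trial does not change how much tissue is collected (Pathology analysis).

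**The concern.** The fallback has to decide whether a particular lesion is malignant. Biochemistry is measured once per patient and time point and is the same for all lesions of that patient. In a patient with confirmed ovarian cancer, a raised tumour-related value is explained by the known cancer, whether or not the focus in question is malignant. If it counts towards the label, all unconfirmed lesions of that patient move the same way: towards malignant when the value is raised, towards benign when it has normalised after neoadjuvant chemotherapy.

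The primary objective is at stake. A FAPI-only lesion receives histology only if routine surgery or biopsy happens to take it. FDG PET/CT belongs to the standard work-up that guides treatment, so FDG-visible lesions can influence what is sampled. FAPI-only lesions can therefore be expected to form a disproportionate share of the unverified ones. Each label assigned there affects both tracers at once. A FAPI-only lesion called malignant is a FAPI true positive and an FDG miss; called benign, it is a FAPI false positive and an FDG true negative.

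**Working it through.** The documents give no number of lesions without histology and no power calculation, so there is no plan figure to reproduce. The counts below are assumptions that show the mechanism and its possible directions.

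**1. Benign lesions labelled malignant.** Assume 60 truly malignant lesions, of which FAPI finds 55 and FDG 45. Let k benign FAPI-only lesions and j benign FDG-only lesions be labelled malignant. Then

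- FAPI sensitivity = (55 + k)/(60 + k + j)
- FDG sensitivity = (45 + j)/(60 + k + j)
- difference = (10 + k − j)/(60 + k + j)

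| k | j | FAPI | FDG | Difference |
|---|---|---|---|---|
| 0 | 0 | 55/60 = 91.7% | 45/60 = 75.0% | 16.7 points (truth) |
| 2 | 0 | 57/62 = 91.9% | 45/62 = 72.6% | 19.4 points |
| 6 | 0 | 61/66 = 92.4% | 45/66 = 68.2% | 24.2 points |
| 6 | 6 | 61/72 = 84.7% | 51/72 = 70.8% | 13.9 points |

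In the third row, with those six as FAPI's only false positives, the true FAPI PPV is 55/61 = 90.2% but is reported as 61/61 = 100%. In the fourth row the same error on the FDG side takes the difference below the truth.

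**2. No true difference.** Assume 100 malignant lesions, 90% sensitivity for both tracers, and 10 benign FAPI-only lesions of which a share f is labelled malignant. The spurious difference is 10f/(100 + 10f):

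- f = 0.25: 2.5/102.5 = 2.4 points
- f = 0.5: 5/105 = 4.8 points
- f = 1: 10/110 = 9.1 points

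With 5 to 20 such lesions and f from 0.25 to 1, the range is 1.25/101.25 = 1.2 points to 20/120 = 16.7 points.

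**3. Malignant lesions labelled benign.** Start from the peritoneal sensitivities that the Background cites from one prospective study, 98% for FAPI and 76% for FDG. Assume that every lesion found by FDG is also found by FAPI, so 22 per 100 are FAPI-only, and that none of these has histology. If y of them are labelled benign, because FDG is negative or the laboratory value has normalised, the difference is (22 − y)/(100 − y) and FAPI PPV is (98 − y)/98:

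- y = 5.5: 16.5/94.5 = 17.5 points, PPV 94.4%
- y = 11: 11/89 = 12.4 points, PPV 88.8%
- y = 22: 0 points, PPV 77.6%

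**4. The two statements of the fallback side by side.** The Study flow overview covers suspicious lesions in general and lists US, MRI and CT. The Diagnostic accuracy section covers FAPI lesions only and adds FDG PET/CT. Biochemistry or laboratory tests appear in both. The listed sources can thus push a FAPI-only lesion either way, and the two sections do not agree on what they are.

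**The case against.** The strongest objection is that laboratory tests are one item in a composite list. Imaging is lesion-level, medical records can be, and nothing says that a blood value decides alone. How the sources are weighed may be set out in the full protocol, and a condensed article need not repeat it. This stands: the lack of a combining rule is not the point here. But no combining rule makes a patient-level value specific to a lesion.

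Secondly, the tests are not named, and follow-up runs for up to 10 years. Once the resected disease is gone, the laboratory course can bear on what remains, read together with imaging. This also stands, and it is why laboratory values may stay as supporting evidence.

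Thirdly, a reader might infer that the rule inflates FAPI, turning benign FAPI-only lesions into true positives. The documents do not support a fixed direction. The statement that "FAPI PET/CT detected far more peritoneal metastases" comes from case reports and concerns true metastases, not benign foci. The same section describes FAP as low or absent in benign conditions and warns that benign conditions can mimic metastases on FDG. FDG-only lesions can be mislabelled too, and an FDG-negative scan in the fallback works against FAPI.

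Lastly, not every recruited patient will have ovarian cancer. The Sample size and patients section puts other malignancies or, rarely, benign conditions at roughly 10–15% of those highly suspected. The argument applies to the 50 confirmed patients.

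**Conclusion.** The concern holds in a limited form. Both sections admit a patient-level value as evidence on single lesions, where it cannot discriminate, in an accuracy comparison made by lesion site. Relying on it there adds error that is shared by all unverified lesions of a patient and that can be expected to fall mainly on FAPI-only lesions. That last step is an inference from the hidden FAPI result and the unchanged tissue sampling; the documents give no count.

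Neither the direction nor the size of the net bias can be determined. In the illustrations, a true 16.7-point difference is reported as anything from 13.9 to 24.2 points, and a true 22-point difference shrinks to between 17.5 and 0. These figures rest wholly on assumed counts and assumed mislabelling. They show that the labels of a few unverified lesions can move the primary comparison, not how far it will move in this trial.

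**What to change.** Reconcile the source lists in the Study flow overview and Diagnostic accuracy sections, and state one rule in both places. Suggested wording:

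*A lesion without histology is classified only when there is evidence specific to that lesion and independent of both tracers: later tissue from the site, or its course on later routine non-PET imaging. Laboratory values may support this evidence but never decide the label. The rule applies equally to FAPI-only and FDG-only lesions. A lesion without such evidence is reported as unverified, and accuracy is given with the unverified lesions counted once all as malignant and once all as benign.*

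Report the unverified lesions by tracer (FAPI-only, FDG-only, both). The two counts do not bound the difference when both tracers have lesions of their own. With six of each in the first illustration, all benign gives 10/60 = 16.7 points and all malignant 10/72 = 13.9. Mixed labels reach from (10 − 6)/66 = 6.1 to (10 + 6)/66 = 24.2.

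The cost is protocol wording and a small table, with no new tests or visits. FAPI images are interpreted only after all patients are enrolled, so the rule can be fixed before any FAPI result is known. The drawback is that more lesions stay unverified, by a number the documents do not allow one to estimate, and the reported range is wider.

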### Study population

#### Sample size and patients

Patients with biopsy-verified OC prior to the gynecological cancer MDT *or* highly suspected to have OC (based on all information presented at the gynecological cancer MDT) will be recruited until a total of 50 patients with histopathologically confirmed OC have been included. The upper limit of recruited patients is set at 60. Recruitment will take place at an outpatient clinic related to the Dept. of Gynecology and Obstetrics Aalborg University Hospital (Aalborg UH) by trained staff in accordance with national requirements [53]. Because an official sample size calculation is not feasible due to former study limitations, e.g., highly selected patients and lack of histopathology of metastases, the desired number of participants is based on the possibility of recruiting patients within 1.5-2 years at our institution, and more importantly, valid estimates of diagnostic accuracy are obtainable with the planned number of patients in an unselected consecutive cohort. Approximately 25 patients are estimated to undergo direct surgery after [^68^Ga]Ga-FAPI-46 PET/CT (Group A), and 25 patients will undergo NACT followed by a second [^68^Ga]Ga-FAPI-46 PET/CT (Group B). The recruitment strategy is based on unpublished clinical data from our institution and from published literature, where approximately 10–15% of the patients with highly suspected OC (based on all available information at MDT) had other non-OC malignancies or rarely benign conditions upon histopathology, e.g., endometriosis, gastric cancer (i.e., Krukenberg tumors), and colorectal cancer [24, 54].

### Study participant eligibility

The inclusion criteria are; (1) Patients newly diagnosed with biopsy-verified OC *or* highly *s*uspected to have OC (based on all the data presented at the gynecological cancer MDT) *and* referred to primary staging with [^18^F]FDG PET/CT; (2) patients deemed resectable and operable at the MDT with or without neoadjuvant chemotherapy; (3) patients considered physically and mentally able to participate in the research project; (4) patients eighteen years or older and able to consent to participate in the project; and (5) patients can read and understand Danish. The main exclusion criteria are: (1) Patients unfit for surgery; (2) patients with recurrent OC; (3) patients with concurrent non-OC malignancies; (4) patients unable to participate in PET/CT; (5) patients with a history of hypersensitivity to [^18^F]FDG or FAPI tracers; (6) pregnant, lactating, or breastfeeding patients or fertile women not using effective contraceptives; and (7) known medical conditions that would significantly decrease the reliability of the data obtained as part of this study. A full set of exclusion criteria can be found at clinicaltrials.gov (NCT05903807) and euclinicaltrials.eu (EU CT: 2023-505938-98-00).

### Imaging procedure

A dose of 200 *±* 50 Megabecquerel (MBq) [^68^Ga]Ga-FAPI-46 will be injected through an antecubital peripheral venous catheter. Patients will be encouraged to per-oral intake of water and instructed to empty their bladder immediately before PET/CT acquisition, which will be performed 30 *±* 5 min after tracer injection—no other patient preparation is needed. Before imaging, a scout scan will be performed to determine the scan area, which will be identical to the [^18^F]FDG PET/CT scan area. First, a low-dose CT scan (2–4 mSv) will be performed immediately followed by PET image acquisition. The scan procedure will last for approximately 25 min, after which the patients can immediately go home. Presently, there are no guidelines on how to perform a FAPI PET. The FAPI PET procedure used in the present study protocol is based on the best available evidence in the published literature and a systematic review conducted by the investigator [55]. The [^18^F]FDG PET/CT scan procedure will be performed in accordance with the dept. of Nuclear Medicines, Aalborg UHs local instructions and international guidelines [56]. Diagnostic ceCT covering the entire PET field-of-view is conducted as part of common clinical practice, both at primary staging and at post-NACT staging, and will be available when interpreting the PET scans.

### Study-related procedures and data analysis

#### Pathology analysis

The clinical trial will not influence the amount of biological material collected from the patients. The surgical specimens will be divided into different containers during surgery and subsequently sent to the Dept. of Pathology, with labels indicating the exact location according to common clinical practice, enabling correct correlation of the histopathology of lesions to the imaging modalities. All surgical specimens will undergo histopathological examination according to routine clinical practice, with additional analyses, including quantitative evaluations of the density and intensity of FAP-expressing tumor cells or CAFs by applying immunohistochemistry. Standardized uptake values (SUVs) in tumor deposits will be compared to tumor characteristics, as determined by pathology, including immunohistochemistry.

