## Background

In Europe, ovarian cancer (OC) ranks as the fifth leading cause of death among female cancer-related fatalities. In 2020, 27,138 new cases were reported, accounting for 4.9% of all female cancer deaths [1]. Seventy-to-80% of all OC patients are diagnosed at advanced stages because symptoms are discrete and often caused by peritoneal metastases [2]. Early detection and complete cytoreduction (no visible disease, R0 resection) or optimal cytoreduction (leaving tumor nodules < 1 cm, R1 resection) are crucial for treatment and survival [3, 4]. Treatment for OC involves curatively intended primary debulking surgery (PDS) followed by adjuvant systemic chemotherapy; however, in advanced stages where complete cytoreduction by PDS is unlikely, interval debulking surgery (IDS) after 2–3 cycles of neoadjuvant chemotherapy (NACT) is the preferred treatment option [5].

Imaging modalities play a crucial role in the clinical work-up of OC patients and are fundamental for efficient diagnosis and correct patient management. In summary, ultrasound (US) is essential for screening and diagnosis, while magnetic resonance imaging (MRI), computer tomography (CT), and [^18^F]fluorodeoxyglucose positron emission tomography ([^18^F]FDG PET) are useful in evaluating the extent of disease [6–9]. Moreover, multiple imaging-based models have been proposed for the preoperative prediction of cytoreducibility. Although these models provide clinically useful information, no single imaging-based prediction model is adequate for accurately predicting the outcome of a surgical procedure [10–13].

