### Study objectives

#### Primary objectives

The primary objectives are to compare the FAPI PET/CT and FDG PET/CT findings in primary tumors, regional lymph nodes and distant metastases to a histopathological reference standard to the sensitivity, specificity, positive predictive value (PPV), and negative predictive value (NPV) of the PET/CTs, both at primary staging and post-NACT staging (i.e., staging after NACT, prior to interval debulking). This will include a comparison of the cancer stage determined by FAPI PET/CT and conventional imaging (including [^18^F]FDG PET/CT) at primary staging and post-NACT staging [50, 51]. The proportions of patients downstaged, having unchanged stage, and being upstaged according to the added FAPI PET/CT will be determined.

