### Study design

#### Study flow overview

This prospective study will comply with the Standard for Reporting Diagnostic Accuracy (STARD) criteria. Good Clinical Practice (GCP) will be followed to the extent that this is a diagnostic test accuracy trial involving an investigational medicinal product (IMP) [52].

Patients with newly diagnosed biopsy-verified OC *or* highly suspected OC (based on all the information presented at the Gynecological Cancer Multidisciplinary Team Conference (MDT)) with operable and resectable disease will be identified at the MDT. Based on the standard diagnostic workup, which includes [^18^F]FDG PET/CT and a diagnostic contrast enhanced CT (ceCT), and in line with national and international guidelines, patients will either go directly to surgery (Group A) or undergo neoadjuvant chemotherapy prior to surgery (Group B). Patients in both groups (A + B) will undergo FAPI PET/CT prior to treatment and within 1 week of receiving the primary FDG PET/CT (Fig. 1). The additional FAPI PET/CT will not interfere with or delay routine diagnostic workup or treatment, and the results of the FAPI PET/CT will not be available to the patient or the treating physician. Patients in Group B will undergo post-NACT-staging with conventional imaging (including [^18^F]FDG PET/CT) 2–3 weeks after NACT. In addition to conventional imaging, an additional blinded FAPI PET/CT will be performed at post-NACT staging.

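### Histological verification may depend on the FDG result but not directly on FAPI, which would bias the sensitivity comparison towards FDG and the specificity comparison against it

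*Protocol article*

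**What the plan says.** The Primary objectives compare FAPI and FDG findings with histopathology and extend "to the sensitivity, specificity, positive predictive value (PPV), and negative predictive value (NPV) of the PET/CTs". The text beneath Fig. 1 states: "Histopathology of the resected specimens and biopsies will serve as a reference standard for calculating the diagnostic accuracy".

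Four further statements settle who knows what when tissue is taken:

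- **FDG is known.** Study flow overview assigns patients to direct surgery or to chemotherapy first as follows: "Based on the standard diagnostic workup, which includes [^18^F]FDG PET/CT and a diagnostic contrast enhanced CT (ceCT").
- **FAPI is not known.** The same section says that "the results of the FAPI PET/CT will not be available to the patient or the treating physician", and Ethical considerations repeats this.
- **FAPI is read late.** Beneath Fig. 1, the FAPI "PET/CT data will be interpreted after enrollment of all patients and compared to the" FDG data.
- **The trial adds no tissue.** Pathology analysis says: "The clinical trial will not influence the amount of biological material collected from the patients". Specimens are labelled by location, but the article mentions no record of why each was taken.

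Suspicious FAPI lesions "lacking histopathological confirmation will be evaluated using available routine diagnostic images", together with records and laboratory tests (Diagnostic accuracy).

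**The concern.** One of the two tests under comparison can influence which sites reach the reference standard, and the other cannot. This is differential partial verification. Malignant sites that FAPI shows and FDG misses carry most of any FAPI sensitivity advantage. They are also the sites least likely to be sampled, unless the surgeon sees them or ceCT shows them. Confining the analysis to sampled sites does not remove the problem, because the selection defines that set.

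The same selection over-represents FDG-positive benign sites, so FDG specificity looks worse than it is. Two measures named in the primary objective could thus be distorted in opposite directions, and a selection artefact could be read as a difference between tracers. This matters because the Background faults earlier studies for lacking histology beyond the primary tumour, and the sample size section relies on valid accuracy estimates being obtainable.

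**Working it through.** The article gives no figure for this effect, so there is nothing to reproduce. The check is an expected-value calculation among sampled sites.

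**Inputs from the document.** The Background cites a prospective study with sensitivities (FAPI vs FDG) of 98% vs 76% for peritoneal metastases and 81% vs 61% for lymph node metastases. The gaps are 22 and 20 points.

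**Assumptions not in the document.** Probability of sampling is *a* = 0.9 if FDG is positive and *b* = 0.8, 0.6 or 0.4 if FDG is negative, with no direct dependence on FAPI. For specificity, the same rates apply to benign sites, and true specificity is 90% for both tracers.

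**Sensitivity.** With true FDG sensitivity *s*:

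- Apparent FDG sensitivity = *a·s* / [*a·s* + *b*(1−*s*)].
- Apparent FAPI sensitivity = [*a*·P(FAPI+, FDG+) + *b*·P(FAPI+, FDG−)] / the same denominator, with probabilities among malignant sites.

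The joint probabilities are taken two ways: the tests detect independently, or every FDG-detected site is also FAPI-detected (nested).

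Peritoneal, *b* = 0.6:

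- Denominator: 0.9×0.76 + 0.6×0.24 = 0.684 + 0.144 = 0.828.
- FDG: 0.684/0.828 = 82.6%.
- FAPI: 98.0% if independent; (0.684 + 0.6×0.22)/0.828 = 98.6% if nested.
- Gap: 15.4 to 15.9 points.

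Nodal, *b* = 0.6:

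- Denominator: 0.9×0.61 + 0.6×0.39 = 0.549 + 0.234 = 0.783.
- FDG: 0.549/0.783 = 70.1%.
- FAPI: 81.0% if independent; (0.549 + 0.6×0.20)/0.783 = 85.4% if nested.
- Gap: 10.9 to 15.3 points.

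**Specificity.** Apparent FDG specificity = 0.9·*b* / (0.9·*b* + 0.1·*a*). For *b* = 0.6: 0.54/(0.54 + 0.09) = 85.7%.

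| Sampling if FDG-negative (90% if FDG-positive) | Peritoneal FDG sensitivity | Peritoneal gap (points) | Nodal FDG sensitivity | Nodal gap (points) | FDG specificity |
|---|---|---|---|---|---|
| 90% (no dependence) | 76.0% | 22.0 | 61.0% | 20.0 | 90.0% |
| 80% | 78.1% | 19.9–20.1 | 63.8% | 17.2–18.6 | 88.9% |
| 60% | 82.6% | 15.4–15.9 | 70.1% | 10.9–15.3 | 85.7% |
| 40% | 87.7% | 10.3–11.3 | 77.9% | 3.1–11.3 | 80.0% |

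If false positives are independent between tracers, FAPI specificity stays at 90%. The false FAPI advantage is then 90.0 − 85.7 = 4.3 points in the 60% row. At a sampling ratio *b*/*a* of 0.5, FDG specificity is 0.45/(0.45 + 0.10) = 81.8%, a false advantage of 8.2 points. It falls to 4.1 points when dependence is halfway to its maximum, and to zero if both tracers give exactly the same false positives.

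**Predictive values.** FDG PPV and NPV do not change, because sampling depends only on the FDG result. FAPI values can. With half of sites malignant (assumed), independent tests, peritoneal sensitivities and a ratio of 0.5, FAPI PPV rises from 90.7% to 94.0% and NPV falls from 97.8% to 96.6%.

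**The case against.** **No passage says that FDG decides what is removed.** A reader might infer this from the fact that FDG guides treatment planning. The documents support only that it may have an influence. The Background gives the surgical aim as "complete cytoreduction (no visible disease, R0 resection"), so visible FDG-negative disease is a target too. ceCT covers the PET field, and some biopsies precede the MDT conference. This stands. It weakens the dependence, but nothing shows that it removes it.

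**The comparison is not tilted towards FDG as a whole.** That reading is also tempting, but it fails: specificity moves the other way, and FDG predictive values do not move under this model.

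**The calculation describes sampled sites only.** The protocol gives unsampled suspicious lesions a classification from other sources, so its final analysis may not be confined to sampled sites. This stands, and it makes the figures illustrative. The use of FDG images to judge unsampled FAPI lesions is a separate problem.

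**The inputs are weak.** The Background itself says that most earlier findings beyond the primary tumour lacked histological comparison. Readers may also use ceCT to call lesions with low uptake malignant, which would reduce discordance between the tracers. Both points stand.

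**Corrections of this kind belong in an analysis plan that is not shown.** This is fair for the analysis methods, and the full protocol may already cover the point. The reason for taking a specimen is different: unless it is recorded at surgery or recoverable from operation notes, no later analysis can use it.

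**Blinding FAPI and adding no tissue are deliberate safeguards.** Agreed; neither is the error.

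**Conclusion.** The point holds as a conditional one. By design, verification can depend on FDG and cannot depend directly on FAPI, and the article describes nothing that would reveal or offset this. If FDG-negative sites are sampled less often, FDG sensitivity is overstated and the FAPI sensitivity advantage understated, while FDG specificity is understated.

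The size cannot be known from the document, and its lower limit is zero. With 90% versus 60% sampling, the peritoneal gap falls from 22 to about 15–16 points and the nodal gap from 20 to about 11–15. Across 80% to 40% sampling of FDG-negative sites, the peritoneal gap runs from about 20 down to 10 and the nodal gap from about 19 down to 3. These figures rest on assumed sampling rates, on cited sensitivities taken as true, and on an analysis of sampled sites only.

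**What to change.** Keep FAPI blinded and take no extra tissue.

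1. **Record the reason.** Add one specimen-form field for each labelled container: routine part of the operation; reported on preoperative imaging; or seen at surgery without an imaging report. Keep the last two separate, because disease found by eye despite negative imaging is verification that did not depend on FDG. Code patients already operated on from operation notes where these allow.
2. **Keep all histology-verified sites in the main comparison.** Restricting it to routine specimens would discard informative nodal and peritoneal disease.
3. **Report the proportion verified** for each FDG/FAPI result combination.
4. **Add two sensitivity analyses.**
   - Sites sampled independently of imaging: routine specimens plus disease seen at surgery without an imaging report.
   - Bounds on the FAPI-minus-FDG differences in sensitivity and specificity, counting all unsampled discordant sites (FAPI-only and FDG-only) as malignant and then as benign. Add the two mixed settings (FAPI-only malignant with FDG-only benign, and the reverse), since these give the outer limits of both differences.

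Inverse-probability weighting is optional. It needs a list of unsampled sites and assumes that sampling depends only on recorded imaging.

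The cost is one form field, a short added analysis and wider stated uncertainty at nodal and peritoneal sites.
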